### Data collection

#### Focus groups with healthcare professionals and patient interviews

For formative assessment in Aim 1, we will conduct focus groups with six PACT team members including PCP, nurse care manager, clinical associate and administrative clerk to assess feasibility and acceptability of MCCP in primary care. We will also conduct 20 individual patient interviews to explore patient perspectives on the proposed intervention.

#### Electronic data extraction and chart reviews

For most measures, we will use automated structured data such as ICD codes, lab values, pharmacy and imaging in the VA electronic health records (Table 1). We will use chart reviews to extract data regarding the primary outcome measure, existence of electronic health record (EHR) progress note documenting a new MASLD diagnosis and complete risk stratification (e.g., fibrosis).

**Table 1 Tab1:** Data sources

Prognostic Measures	Measures/Sources	Baseline	6 Months	12 Months
Demographics	CDW	✓		
Medications (liver and non-liver)	CDW	✓		
Comorbidities	CDW	✓		
VA healthcare utilization	CDW	✓		
Adherence to ambulatory care	CDW	✓		
Outcomes				
MASLD detected and risk stratified*	CDW/EHR	✓	✓	
Testing with Fibroscan	CDW	✓	✓	✓
Referral for hepatology	CDW consult table	✓	✓	✓
Seen in hepatology clinic	CDW	✓	✓	✓
Documentation of MASLD discussion	Chart review		✓	✓
Referral to weight loss services	CDW consult table	✓	✓	✓
Enrollment in weight loss services	CDW	✓	✓	✓

*CDW* corporate data warehouse, *EHR* electronic health record

*primary outcome measure

#### Interviews with healthcare professionals and patients

For summative evaluation in Aim 3, we will conduct interviews with six PCPs and six nurses in the MCCP arm and three PCPs and three nurses in the usual care arm. These interviews will query aspects of adoption and implementation, such as barriers and facilitators to the referral process and adaptations made while delivering the intervention.

#### Data quality and storage

We will verify the study outcome using data from the *Compensation and Pension Record Interchange (CAPRI)*, which provides access to all VA text notes, including progress notes, pathology, and imaging reports. We have used CAPRI for several studies, including to examine the validity of NAFLD diagnosis, NAFLD care, and cirrhosis diagnosis and care. Personal and health information about study participants will be securely stored on secure servers and/or locked cabinets before, during, and after the study in accordance with institutional and IRB guidelines.

### Sample size

Over the study period, we anticipate including ~ 8000 patients in the intervention arm and ~ 8000 in the usual care control arm. We estimated sample size and power for the parallel, cluster-randomized trial based on the number of clusters (8 per arm) to detect the anticipated effect size in the percentage of MASLD detected and risk stratified (7% for usual care vs. 17% for MCCP) with the intracluster correlations coefficients (ICC) as large as 0.04. To account for dependency among patients within a PACT, the design effect was applied following the approach of Killip et al. [25]. Applying this adjustment, with 16 total PACTS there is 84% to 99% power to detect a difference of 7% versus 17% with ICCs ranging from 0.02 to 0.04. In the event PACT attrition in the MCCP group is as high as 2 (attrition is not possible in the usual care arm), there is 80% to 99% power to detect desired effects with ICCs 0.02 to 0.04.

### Data analysis

#### Analysis plan for formative assessment

Qualitative data from PACT focus groups and patient interviews will be analyzed using rapid analysis [26] to allow the research team to move through qualitative data analysis in a timely manner to produce rigorous findings that will inform MCCP intervention adaptation. The qualitative methodologist will summarize transcripts using a template designating content into CFIR constructs. Summaries will identify emergent themes and key insights from interviews to be captured and documented. For focus group summaries, the role of the different providers will be noted alongside text to track source and allow analysts to consider how position could influence perspective. We will use matrixes to explore similarities, differences and patterns in experiences with screening and MASLD care across PACT teams and patients.

#### Analysis plan for cluster-randomized trial

We will compare baseline outcome variables for demographics (e.g., age, gender, race), medications (e.g., diabetes, dyslipidemia, hypertension), comorbidities (i.e. metabolic conditions, other medical or mental health conditions), healthcare utilization (e.g., outpatient, inpatient encounters), and adherence to ambulatory care for the MCCP versus usual care participants using SAS Proc Mixed for continuous variables and SAS Proc Glimmix for categorical variables. We will also compare baseline PACT characteristics (e.g. number of clinician and provider mix) between the study groups. Variables that differ between the study groups will be included as covariates in subsequent outcome analyses. Outcome analyses will be performed at 6- and 12-months post-enrollment for both primary (i.e. dichotomous composite of a new MASLD diagnosis and risk stratification) and secondary (i.e. testing with Fibroscan, referral for hepatology/weight loss services) outcomes. Intention -to-Treat and Per-Protocol analyses will employ multilevel models that account for dependency of patients within PACTs. SAS Proc Glimmix will be used for each dichotomous outcome with study group (MCCP or usual care) as the main predictor and variables that differ between study group at baseline will be included as covariates.

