## Methods

### Study design

A two-arm, parallel, cluster-randomized trial will assess the effect of a MCCP intervention comprised of an e-trigger and structured provider education on the MASLD screening, diagnosis, referral, and treatment. Clusters are VA patient-centered primary care clinics, called Patient Aligned Care Teams (PACTs). The trial will randomize 16 PACTs in a 1:1 allocation ratio to two arms: MCCP intervention versus usual care. These 16 PACTs will be randomly selected from the 37 eligible PACTs, excluding those participated in focus groups. We will also conduct mixed-methods formative and summative evaluations of the intervention throughout the 4 years of the study. The study is designed with pragmatic features to foster efficient implementation of findings into clinical care settings. Figure 1 depicts the study design and procedures.

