### Study setting

The study will take place at the Michael E. DeBakey VA Medical Center (MEDVAMC) in Houston, Texas, which provides care for more than 111,000 Veterans and has a total of 37 PACTs. The typical PACT core team consists of a primary care provider (physician, nurse practitioner, or physician assistant), a nurse care manager (registered nurse), a clinical associate (practice nurse or health technician), and a clerk. Teams work closely with multidisciplinary professionals including pharmacists, social workers, nutritionists, and specialist providers. The study and principal investigators will be introduced to the PACT’s lead primary care providers (PCP) during department meetings. Those who are interested will be recruited to advise on the feasibility and acceptability of the intervention.

Specialized PACTs such as infectious disease, spinal cord injury, homeless, and geriatrics are excluded due to patients facing more pressing issues. The Post-deployment PACT is excluded due to unique care needs and having only one team. We also exclude PACTs with fewer than 100 patients expected in the three-month period. Additionally, unstable PACT leadership (e.g., pending departure or vacancy) at the time of randomization will be excluded. The biostatistician will randomize PACTs into the intervention or usual care groups with a computer-generated randomization.

### Participants in specific aim 1

To understand the feasibility and acceptability of the e-trigger, the research team will identify a random sample of patients with already diagnosed MASLD and receiving care at MEDVAMC within the past year using electronic health record search and chart review. Phone call visits are excluded as they are typically brief, addressing lab results or medication changes. Potential participants will be contacted during a clinic encounter to determine interest in participating. Patients who agree to participate will be scheduled for a telephone/video interview. We will recruit patients on a rolling basis until we reach our sample goal of 20 patients or reach saturation in the themes patients are reporting. Six PACTs will be interviewed to understand the barriers and facilitators to implementing the e-trigger.

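### Covariates for the primary and secondary models are chosen by observed baseline difference, so the model is unknown until the arms are compared and precision from a prognostic covariate is left to chance

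*Protocol article*

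**What the plan says.** The rule is in the protocol article, section Analysis plan for cluster-randomized trial. The arms are first compared on patient variables ("We will compare baseline outcome variables for demographics (e.g., age, gender, race), medications (e.g., diabetes, dyslipidemia, hypertension", followed by comorbidities, utilisation and adherence to ambulatory care). PACT variables come next: "We will also compare baseline PACT characteristics (e.g. number of clinician and provider mix) between the study groups". The consequence follows: "Variables that differ between the study groups will be included as covariates in subsequent outcome analyses". The last sentence of the section repeats it for the Glimmix model of each dichotomous outcome: "variables that differ between study group at baseline will be included as covariates". The article gives no threshold for a difference, no fixed list and no limit on the number of covariates.

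Three other places bear on the point:
- Study design: "The trial will randomize 16 PACTs in a 1:1 allocation ratio to two arms: MCCP intervention versus usual care".
- Study setting: "The biostatistician will randomize PACTs into the intervention or usual care groups with a computer-generated randomization", with no balancing factor described.
- Table 1 ticks the primary measure, "MASLD detected and risk stratified", at baseline. The analysis section neither lists it among the compared variables nor commits to adjusting for it.

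**The concern.** A covariate improves a randomised comparison when it predicts the outcome. Whether its arm means happen to differ is a separate matter, and the rule selects on the second. This has two consequences.

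1. **The primary model depends on the data.** Its covariates are settled only after the arms have been compared. With the usual logit link (assumed; the article names only the procedure), the conditional odds ratio also changes with the covariate set, so the quantity being estimated is open until then.
2. **Precision is left to chance.** A strong predictor that happens to balance is left out, and a variable unrelated to the outcome enters if it happens not to balance. With 16 randomised units, PACT-level prognostic information is where most of the available precision lies.

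**Working it through.** **The plan's own power figure.** Inputs from the Sample size section: 7% v 17%, 8 PACTs per arm, ICC 0.02 to 0.04, stated power 84% to 99% (80% to 99% if two MCCP PACTs are lost). Two-sided alpha 0.05 and patients per PACT, m, are not stated with the power figure and are assumed. The effective sample size per arm is 8m/[1+(m−1)ICC].

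At m = 500 and ICC 0.04:
- Design effect 1 + 499×0.04 = 20.96, effective n = 4000/20.96 = 190.8.
- Pooled SE √(2×0.12×0.88/190.8) = 0.0333; unpooled SE √((0.07×0.93+0.17×0.83)/190.8) = 0.0329.
- Power = Φ[(0.10 − 1.96×0.0333)/0.0329] = 85.5%.

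The same method gives 98.7% at ICC 0.02, and 80.6% and 97.2% with 6 v 8 PACTs. All four are within 2 points of the stated figures. Any m from 430 to 720 reproduces them that closely. At m = 1000 (the section says "we anticipate including ~ 8000 patients in the intervention arm and ~ 8000 in the usual care control arm", and 8000/8 = 1000) the results are 86.3%, 99.0%, 81.5% and 97.7%. The stated figure does not depend on covariates.

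**How often something enters by chance.** The named items come to about 11 patient-level (3 demographic, 3 medication, 2 comorbidity, 2 utilisation, 1 adherence) and 2 PACT-level. With independent tests at an assumed p<0.05 that respect clustering:
- 2 candidates: 1 − 0.95² = 10%
- 11 candidates: 1 − 0.95¹¹ = 43%
- 13 candidates: 1 − 0.95¹³ = 49%

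**Degrees of freedom.** There are 16 − 2 = 14 between-PACT df, less one for each PACT-level covariate. At ICC 0.04 and m = 500, power from a t reference is 80.7% on 14 df, 79.7% on 12 and 78.3% on 10. Two PACT-level covariates therefore cost about 1 point and four about 2.4. Patient-level covariates cost essentially none, because their slopes are estimated mostly within PACTs.

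**Simulation of the rule.** Setting: 8 v 8 PACTs, 7% v 17%, ICC 0.04, m = 500, 8000 trials per setting (Monte Carlo SE about √(0.8×0.2/8000) = 0.4 points), t-tests on the correct df. One PACT-level candidate is prognostic and explains an assumed share of between-PACT variance. The others are noise. A candidate enters if its arm difference has p<0.05.

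| PACT-level candidates | Share | Unadjusted | Plan's rule | Prognostic one fixed in advance |
|---|---|---|---|---|
| 2 | 0.1 | 80.9% | 79.9% | 81.4% |
| 2 | 0.3 | 80.5% | 80.0% | 88.8% |
| 2 | 0.5 | 80.7% | 80.9% | 96.0% |
| 5 | 0.1 | 81.2% | 77.0% | 81.3% |
| 5 | 0.3 | 80.2% | 77.1% | 88.6% |
| 5 | 0.5 | 81.1% | 78.4% | 96.0% |

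The prognostic covariate was selected in 4.9% to 5.3% of trials, as expected when selection ignores prognosis. The loss with five candidates exceeds the df cost because a covariate enters precisely when it is correlated with arm, and that inflates the variance of the arm effect. With no treatment effect, rejection under the rule was 3.8% to 4.2% against a nominal 5%.

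**The case against.** The strongest reply is that adjusting is sensible here and that the rule does little harm. Chance imbalance is likely with 16 PACTs. At ICC 0.04 and 7% the between-PACT SD is √(0.04×0.07×0.93) = 0.051, and the SE of an arm difference in PACT rates is 0.051×√(2/8) = 2.55 points. A gap above 2.5 points then occurs in about one trial in three. This stands, but it supports adjustment for named covariates rather than selection by observed difference.

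Several stronger readings are tempting, and the documents do not support them.
- **A large power loss from the rule.** If 12 candidates were all PACT-level, simulated power would fall from about 80% to about 72%. The article names only two PACT characteristics; the other named items are patient-level.
- **Exhausted between-PACT df.** Only PACT-level covariates draw on the 14, at about 1 point of power for two.
- **Inflated type I error.** A fixed screen is slightly conservative.
- **The baseline rate as the best predictor.** The outcome is a new diagnosis, and no document says how well a PACT's baseline rate predicts it.
- **Every baseline difference is chance.** That is too absolute for the analysed sets. Patients enter through scheduled visits, PACT attrition is possible only in the MCCP arm, and per-protocol analyses are planned.

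It is also fair that p<0.05 is an assumption, that the planned power never relied on adjustment, and that the gain matters mainly at the upper ICC. At ICC 0.02 and m = 500, power on 14 df is already 97.4%.

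The reply that covariates belong in an unseen analysis plan does not stand. The article commits to a rule, twice.

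**Conclusion.** The point holds as a weakness of prespecification with forgone precision, and it should be fixed. It is not a validity failure. Two parts are firm: the primary model is undefined until the arms are compared, and selection is unrelated to prognostic value.

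The size rests on assumptions: a p<0.05 screen, m = 500, ICC 0.04, and a prognostic share that no document gives. On these, fixing the covariate in advance is worth roughly 0, 8 or 15 points of power over no adjustment at shares of 0.1, 0.3 or 0.5. The rule captures almost none of that gain. Its own cost is 0 to 1 point with the two PACT characteristics named and about 3 to 4 with five.

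**What to change.** In the section Analysis plan for cluster-randomized trial, delete the selection rule in both sentences. Replace it with one short covariate set, named in advance and used in every primary and secondary outcome model. An example is the PACT-level baseline rate of the primary measure (already planned in Table 1) plus a few patient-level predictors chosen on clinical grounds, with PACT-level terms limited to one or two. State that baseline differences are reported descriptively and play no part in choosing covariates.

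The cost is wording; the baseline data are already planned. Each PACT-level term uses one of the 14 between-PACT df, and the gain is near zero if the chosen covariate is only weakly prognostic.

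### The stated power uses large-sample critical values although only 16 PACTs carry the comparison; with 14 or 12 degrees of freedom it is lower, and the two-PACT-loss case falls below 80%

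*Protocol article*

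**What the plan says.** Under Study design: "The trial will randomize 16 PACTs in a 1:1 allocation ratio to two arms: MCCP intervention versus usual care". Under Sample size, power is "based on the number of clusters (8 per arm) to detect the anticipated effect size", namely "7% for usual care vs. 17% for MCCP". A design effect is applied for the dependency of patients within a PACT, and the result is that "there is 84% to 99% power to detect a difference of 7% versus 17% with ICCs ranging from 0.02 to 0.04". The same paragraph gives 80% to 99% if two MCCP PACTs are lost. On numbers: "we anticipate including ~ 8000 patients in the intervention arm and ~ 8000 in the usual care control arm". Alpha, sidedness, patients per PACT and the reference distribution behind the power figures are not given there.

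Under Analysis plan for cluster-randomized trial, multilevel models with PACT as the clustering level are planned, and "SAS Proc Glimmix will be used for each dichotomous outcome with study group (MCCP or usual care) as the main predictor". Baseline variables that differ between groups, after a comparison that includes PACT characteristics, enter as covariates. No denominator df method is named.

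**The concern.** A whole PACT receives one treatment or the other, so the precision of the study-group effect is judged from variation among 16 PACTs. With 8 against 8, that variation is estimated on 14 degrees of freedom; with 8 against 6, on 12. A design effect enlarges the variance correctly. If the effective patients are then treated as independent and a normal critical value is used, the uncertainty in the between-PACT variance is left out.

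Two things are at stake. The published assurance of at least 80% power after losing two PACTs may not hold. And if the same large-sample habit carried into the primary model, intervals would be too short and the test would reject too often.

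**Working it through.** **Inputs.** 8 PACTs per arm, 7% vs 17%, ICC ρ of 0.02 and 0.04, loss of two MCCP PACTs, about 8,000 patients per arm (all from Study design and Sample size). Hence m = 8,000/8 = 1,000 patients per PACT.

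**Assumptions.** Two-sided alpha 0.05, equal PACT sizes, common ICC.

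**Step 1: reproduce the stated power.** Design effect DE = 1 + (m − 1)ρ; effective patients in an arm of k PACTs = k·m/DE. At ρ = 0.04, DE = 1 + 999 × 0.04 = 40.96, giving 8,000/40.96 = 195.3 per arm.

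- Unpooled SE = √[(0.07×0.93 + 0.17×0.83)/195.3] = √(0.2062/195.3) = 0.0325.
- Pooled SE = √(2×0.12×0.88/195.3) = 0.0329.
- Normal approximation: Φ[(0.10 − 1.96×0.0329)/0.0325] = 86.3%.

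The other cases follow in the same way (table). At m = 1,000, three of the four stated figures come within 2 points; the 84% is missed by 2.3. At m = 500 the results are 85.5%, 98.7%, 80.6% and 97.2%, all within 2 points of the stated 84%, 99%, 80% and 99%. The stated ranges are therefore of the normal-approximation kind, though the PACT size used cannot be recovered.

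**Step 2: replace the normal with t.** Noncentrality λ = 0.10/SE.

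- 8 vs 8, ρ = 0.04: λ = 0.10/0.0325 = 3.08, critical value 2.145 (14 df). Noncentral t gives 81.6%, or 81.0% with the pooled SE under the null.
- 8 vs 6, ρ = 0.04: effective patients 195.3 and 6,000/40.96 = 146.5. SE = √(0.0651/195.3 + 0.1411/146.5) = 0.0360, λ = 2.78, critical value 2.179 (12 df). Power is 72.3%, or 74.9% with the pooled SE.

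Power at m = 1,000. The last column is a t-test on PACT proportions with beta-binomial data, 200,000 runs.

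| PACTs | ICC | Stated | Normal | Noncentral t | Simulated t-test |
|---|---|---|---|---|---|
| 8 vs 8 | 0.04 | 84% | 86.3% | 81.0-81.6% | 82.9% |
| 8 vs 8 | 0.02 | 99% | 99.0% | 97.7-97.9% | 98.0% |
| 8 vs 6 | 0.04 | 80% | 81.5% | 72.3-74.9% | 77.4% |
| 8 vs 6 | 0.02 | 99% | 97.7% | 94.5-95.4% | 96.0% |

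**Step 3: can more patients help?** As m grows, the effective number tends to k/ρ. At ρ = 0.04 that is 8/0.04 = 200 and 6/0.04 = 150. Noncentral t then gives 73-76% for 8 vs 6. The same simulation with no sampling error within PACTs (unlimited patients) gives 78%. Both stay below 80%. For 8 vs 8 the noncentral-t ceiling is about 82-83%.

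**Step 4: the primary test, if large-sample.** 2·P(t₁₄ > 1.96) = 7.0%; with 12 df it is 7.4%. Simulated null rejection of the PACT-level statistic at the 1.96 cut-off is 6.8% (8 vs 8) and 7.0-7.1% (8 vs 6). A Wald z from a random-intercept logistic model gives 7.5-8.5% (about 700 to 1,000 runs per setting), falling to 5.0-6.3% with a t₁₄ cut-off. The interval half-width ratio is 1.96/2.145 = 0.91, so large-sample intervals would be about 9% too short.

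**The case against.** Four points can be made for the plan.

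- **Clustering is handled.** A reader might infer that the plan ignores its small number of clusters. It does not: power is built from 8 clusters per arm with a design effect and a cluster-loss scenario, and the model includes PACT. Only the small-sample reference distribution is absent. This stands in full.
- **The 7% is not a stated property of the plan.** A reader might take it as the actual error rate. The article names a procedure but no test statistic, df option or random-effect coding, and the df the procedure would use depends on that coding. A journal article may also leave this to the full protocol or SAP. This stands: the 7% is conditional.
- **The full design barely changes.** The loss against the stated 84% is 1 to 3 points, and simulations that include a logit-scale analysis span 82.7-84.9%. This stands: the full-design figure is slightly optimistic at most.
- **The eligibility floor is not the planned size.** It is tempting to compute power at 100 patients per PACT, since "We also exclude PACTs with fewer than 100 patients expected in the three-month period". That is a minimum for entry over three months, and the shortfall at that size is partly cluster size: the normal approximation itself gives only 79.2% at ICC 0.04. It cannot be set against a figure for about 16,000 patients.

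None of this rescues the two-PACT-loss figure. The article publishes that number itself, so it has not been left to another document.

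**Conclusion.** The concern holds for the power statement. The firm part is the loss of two MCCP PACTs at ICC 0.04: about 72-77% against the stated 80%, with no recovery from larger PACTs. At ICC 0.02 that scenario has about 95-96% against the stated 99%. The full design has about 81-83% and 98% against 84% and 99%, a small difference.

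That normal critical values were used is inferred from how the figures reproduce; the article does not say so. The results rest on the assumptions listed above. Unequal PACT sizes would lower power further.

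For the primary model, the point is a precaution: the df method should be fixed in advance, because large-sample inference would carry a type I error of about 7%.

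**What to change.** 1. In Sample size, restate both power ranges with a t reference, using 14 df for 8 vs 8 and 12 df for 8 vs 6, and give the patients per PACT, alpha and sidedness used.
2. In Analysis plan for cluster-randomized trial, specify a small-sample denominator df for study group (Kenward-Roger or between-within), reduced for any PACT-level covariates, with t-based confidence intervals. Settle this before outcome data are seen. A PACT-level t-test or permutation test on PACT proportions would be a useful check.

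The cost is one model option, a sentence or two of text and a recalculation. Stated power falls slightly for the full design and below 80% in the two-PACT-loss case at ICC 0.04. Intervals become about 9% wider (2.145/1.96 = 1.09) than large-sample ones with 14 df.

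### Outcomes are scheduled at baseline, but a PACT's own baseline rate has no fixed place in the outcome models; always adjusting for it is a cheap gain if it predicts follow-up moderately well

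*Protocol article*

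**What the plan says.** All places are in the protocol article.

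- **Data collected.** In Table 1 the primary measure, "MASLD detected and risk stratified", is ticked at baseline and at 6 months. Fibroscan testing, the two hepatology rows and the two weight-loss rows are ticked at baseline, 6 and 12 months. The row for a documented discussion of MASLD has no baseline tick.
- **Model.** Under *Analysis plan for cluster-randomized trial*: "SAS Proc Glimmix will be used for each dichotomous outcome with study group (MCCP or usual care) as the main predictor". Covariates are the variables found to differ between the arms at baseline. The models are multilevel, with patients within PACTs.
- **Variables compared.** Demographics, medications, comorbidities, utilization and adherence to ambulatory care are listed. For the PACT level: "We will also compare baseline PACT characteristics (e.g. number of clinician and provider mix) between the study groups". No baseline outcome rate is named.
- **Outcome definition.** Under *Outcomes*, the primary outcome requires a new diagnosis together with completed risk stratification.
- **Size and power.** "The trial will randomize 16 PACTs in a 1:1 allocation ratio to two arms: MCCP intervention versus usual care"; "we anticipate including ~ 8000 patients in the intervention arm and ~ 8000 in the usual care control arm"; and "there is 84% to 99% power to detect a difference of 7% versus 17" percent, for ICCs of 0.02 to 0.04.

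**The concern.** In a trial of 16 large clusters, the precision of the arm comparison is set almost entirely by how much PACTs differ from one another. Patient-level covariates help mainly where they explain differences in PACT case mix. A PACT's earlier rate of detecting and stratifying MASLD bears directly on those differences. The document schedules baseline values of most outcomes, yet its model gives them no assured role.

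The stated covariate rule does not do this job. It admits a variable because the arms happen to differ on it. A strongly prognostic PACT rate that is well balanced would be left out, and a weakly prognostic variable that is imbalanced by chance would be put in. At stake is the width of the interval for the primary effect and for each secondary effect with a baseline value, mainly toward the upper ICC that the sample size section allows for.

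**Working it through.** **Inputs**

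- 8 PACTs per arm (*Study design*, *Sample size*).
- m = 8,000 / 8 = 1,000 patients per PACT (*Sample size*). The cluster size used in the power calculation is not stated. The only stated floor is in *Study setting*: "We also exclude PACTs with fewer than 100 patients expected in the three-month period".
- Rates: "7% for usual care vs. 17% for MCCP"; ICC 0.02 to 0.04 (*Sample size*).
- Assumed: two-sided 5% (no alpha is stated), and r, the correlation between PACTs' baseline and follow-up rates, from 0 to 0.7 (the document gives none).

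**1. The plan's own power.** Effective n per arm = 8m / [1 + (m − 1)ICC], then a normal-approximation test of two proportions.

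| | ICC 0.04 | ICC 0.02 |
|---|---|---|
| Stated, 8 vs 8 | 84% | 99% |
| m = 500 | 85.5% | 98.7% |
| m = 1,000 | 86.3% | 99.0% |
| Stated, two MCCP PACTs lost | 80% | 99% |
| m = 500 | 80.6% | 97.2% |
| m = 1,000 | 81.5% | 97.7% |

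The stated figures are reproduced within about 2 points, without any baseline adjustment.

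**2. Where the variance lies.** Between-PACT share = ICC / [ICC + (1 − ICC)/m].

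- ICC 0.04: 0.04 / (0.04 + 0.00096) = 0.977
- ICC 0.02: 0.02 / (0.02 + 0.00098) = 0.953

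**3. Unadjusted comparison on 14 df, ICC 0.04.**

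- Design effect = 1 + 999 × 0.04 = 40.96.
- Variance = (0.07 × 0.93 + 0.17 × 0.83) × 40.96 / 8,000 = 0.2062 × 40.96 / 8,000 = 0.001056, so SE = 0.0325.
- 95% half-width = 2.145 × 0.0325 = 0.070, or 7.0 points.
- Noncentral-t power = 81.6%.

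**4. Adjusted for one PACT-level baseline rate, 13 df.** Multiply the variance by (1 − r²) × (1 + 1/12). The second factor is the cost of estimating the slope from 16 PACTs (1/(K − 4) with K = 16). The interval ratio is √[(1 − r²)(13/12)] × (2.160/2.145).

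| r | Power | Half-width (points) | Interval vs unadjusted |
|---|---|---|---|
| not used | 81.6% | 7.0 | – |
| 0 | 78.0% | 7.3 | 5% wider |
| 0.3 | 81.7% | 7.0 | same |
| 0.5 | 88.4% | 6.3 | 9% narrower |
| 0.7 | 96.8% | 5.2 | 25% narrower |

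Break-even is where the ratio equals 1: r = √[1 − (2.145/2.160)² / (13/12)] = 0.30.

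**5. Sensitivity.**

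| Setting | Unadjusted | r = 0.3 | r = 0.5 | r = 0.7 |
|---|---|---|---|---|
| ICC 0.04, two MCCP PACTs lost, m = 1,000 | 72.3% | 71.5% | 79.5% | 92.1% |
| ICC 0.04, 8 vs 8, m = 100 | 73.9% | 74.0% | 81.8% | 93.5% |
| ICC 0.02, 8 vs 8, m = 1,000 | 97.9% | 97.9% | 99.3% | over 99.9% |

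At ICC 0.02 power is already high, so any gain there is mainly a narrower interval.

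**The case against.** The strongest reply has four parts.

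- **The rule does not exclude the covariate.** A reader might infer that no model can ever use a baseline outcome rate. The document does not support that. The PACT characteristics are given as examples, and a PACT's prior rate could be counted among them and enter if it differed between arms. What stands is that its inclusion is left to chance imbalance.
- **The data may not be in hand.** A reader might infer from Table 1 that the covariate is already collected and merely ignored. For the primary outcome that is not established. The baseline tick is not defined. It may record existing status of enrolled patients, so that a later diagnosis can be called new, and not a prior-period PACT rate. This stands, and it is why the fix includes a definition.
- **Precision is not lost for nothing.** Adjustment spends a degree of freedom and adds slope-estimation error. Below a correlation of about 0.3 it does not help, and at zero it costs 81.6 − 78.0 = 3.6 points of power. This stands; the benefit is conditional on an unknown correlation.
- **The stated analysis is valid, and this is a condensed article.** A multilevel model without a baseline rate is not wrong. The stated power does not rely on adjustment and is reproduced. Fuller covariate detail may sit in an unseen analysis plan. The first two statements stand. The last does not dispose of the point, because the article states a specific covariate rule, and it is that rule which can be improved.

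**Conclusion.** The point holds as a recommended improvement, not as an error that invalidates the analysis. Baseline values are scheduled for the primary measure and five other outcomes. The stated model does not assure any use of a PACT's baseline rate, and the covariate rule is a poor substitute because it does not select on prognostic strength.

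At the upper ICC with 8 PACTs per arm, the likely effect runs from a loss of 3.6 points of power (r = 0) through no change (r about 0.3) to gains of about 7 points (r = 0.5) and 15 points (r = 0.7), with intervals 9% and 25% narrower at the last two. These figures rest on about 1,000 patients per PACT, a two-sided 5% level, the stated 7% and 17%, and an assumed range for the correlation.

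A reader might conclude that the trial needs this adjustment to be adequately powered. By the document's own calculation it does not. The shortfall below 80% after PACT loss appears only when the small number of PACTs is allowed for with a t distribution.

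**What to change.** In *Analysis plan for cluster-randomized trial*, before outcome data are seen:

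1. State that each outcome with a baseline value in Table 1 is always adjusted for the PACT's pre-randomization rate of that same outcome, whatever the observed balance. Exempt the documented-discussion outcome, which has no baseline value.
2. State that the arm effect is tested on between-PACT degrees of freedom: 13 with 16 PACTs and this one PACT-level covariate.
3. For the primary outcome, define the covariate as a PACT rate over a named prior period in comparable patients. A patient's own baseline status cannot serve, since someone already diagnosed cannot have a new diagnosis. A version coded from the Corporate Data Warehouse is enough for a covariate and avoids extra chart review.
4. Say what the Table 1 baseline tick for the primary measure records.

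Cost: a few lines of text, one degree of freedom, and possibly one data-warehouse query. The risk is the small loss of power shown above if PACT rates turn out to be nearly uncorrelated over time.
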